### Outcome measure hierarchy

#### Primary outcome measure

- HDRS (after 18 weeks of treatment).

#### Secondary outcome measures

- SCL-90-R (GSI- score after 18 weeks of treatment).

- The proportion of patients who achieve remission (after 18 weeks of treatment). We have, pragmatically, chosen to define remission as HDRS below 8 [42].

- BDI II (after 18 weeks of treatment).

- WHO 5 (after 18 weeks of treatment).

#### Other outcome measures

- Adverse events. We will classify adverse events as serious or non-serious. Serious adverse events are defined as any medical occurrence that is life threatening, results in death, or persistent or significant disability, or any medical event, which might jeopardise the patient, or require intervention to prevent it [43]. All other adverse events (that is, any medical occurrence not necessarily having a causal relationship with the treatment, but did, however, cause discontinuation of the treatment) are considered as non-serious.

- Scores on HDRS, BDI, SCL 90-R, WHO 5 after 26 weeks of treatment.

- DAPP-BQ.

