### Assessments

Before randomisation: Hamilton Rating Scale for Depression (HDRS) [37], Symptom Checklist 90 Revised (SCL 90-R) [38], Beck’s Depression Inventory (BDI II) [31], World Health Organisation-Five Well-being Index 1999 (WHO 5) [39], Structured Clinical Interviews for DSM-IV Disorders (the depression section of SCID I and SCID II) [30,40], Dimensional Assessment of Personality Pathology-Basic Questionnaire (DAPP-BQ) [41], use of medication, age sex, marital status, and education level.

After 9 weeks of intervention: BDI II WHO 5, use of medication, suicide attempts, and suicides during the intervention period.

After 18 weeks of intervention (end of intensive treatment): HDRS, BDI II, WHO 5, SCL 90-R, use of medication, suicide attempts, and suicides during the intervention period.

After 26 weeks of follow-up treatment: HDRS, SCL 90-R, DAPP-BQ, BDI II, WHO 5, suicide attempts, and suicides during the intervention period.

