### Sample size

With a ‘minimal relevant mean difference’ (MIREDIF) between the two compared interventions of 5 HDRS points, an alpha of 0.05 (type I error), a power of 0.90 (type II error of 10%), and a standard deviation (SD) = 7, the sample size calculation shows that a total of 84 participants are necessary. The calculation is performed using the program “Power and sample size calculations”, version 2.1.31.

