### Ethical considerations and regulatory approval

There are no immediate ethical problems regarding this trial. Research has not identified any significant adverse effects or risks from either of the compared interventions — and we do not know which is the best intervention. During the trial period any adverse event will be reported. The trial has obtained approval by the Regional Ethics Committee of Zealand (no: SJ-43), and is registered at the Danish Data Protection Agency (no: 2008-58-0020).

Participants will be informed of the trial in writing and verbally, and written informed consent will be obtained from every participant before inclusion. All trial participants may, on request, be permitted access to further information about the project. The individual therapists and the principal investigator will perform this function. No expense allowance is offered to trial participants.

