## Discussion

Our protocol has a number of strengths. First, a trial protocol was registered before randomisation began (ClinicalTrials.gov; no.: NCT01070134). In this protocol the outcome hierarchy and analyses plans were presented and these are published in this present publication. Secondly, the trial protocol has been developed according to good clinical research practice enabling the randomised trial to be conducted with low risk of bias and a high degree of external validity [47-50]. Thirdly, the participants in this trial will be similar to patients normally referred to a psychiatric outpatient clinic, and clinicians can therefore more easily relate the results from this trial to a given clinical context. Fourthly, both interventions will be conducted using manuals and adherence to the treatment manuals will be tested. This makes it possible to implement the interventions in clinical practice, and the two interventions can be assessed in future trials. Moreover, we have used the most commonly used outcome measure in trials assessing the effects of psychotherapeutic interventions for depression (HDRS) [28,37,44,51], as well as other clinically relevant outcome measures (e.g., quality of life, suicide attempts, suicides). The two treatments uses about the same resources, so economical considerations seem less important in the choice between the two.

Our trial protocol has a number of limitations. Due to practical circumstances we have planned to include a limited number of trial participants. This will evidently increase the risk of random errors (‘play of chance’). In calculating our sample size we have used a ‘minimal relevant mean difference’ (MIREDIF) of five HDRS points between the two interventions. Former systematic reviews have shown much less differences in effects sizes between compared interventions for depression [44,51,52]. It could be argued that we have set our presumed MIREDIF unrealistically high. However, as experienced Hamilton interviewers we believe that five HDRS points is a reasonable MIREDIF between the two interventions. A smaller mean difference between two interventions will have limited clinical relevance.

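### Non-serious adverse events are defined as those that stopped treatment, so an event that is neither serious nor treatment-ending is not counted, although the article promises to report any adverse event

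*Protocol article*

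**What the plan says.** Adverse events head the list under Other outcome measures in the protocol article. The scheme has two classes only: "We will classify adverse events as serious or non-serious". The serious class covers events that are life threatening, fatal or disabling, and extends to "any medical event, which might jeopardise the patient, or require intervention to prevent it". Everything else is assigned to the non-serious class, which a bracket then explains as "any medical occurrence not necessarily having a causal relationship with the treatment, but did, however, cause discontinuation of the treatment".

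The section on ethical considerations and regulatory approval makes a broader commitment: "During the trial period any adverse event will be reported". It places no limit on the kind of event.

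**The concern.** The bracket works as a definition, not as an example. It makes ending treatment a condition for a non-serious event to exist. The scheme offers no third class, so an event that fails the serious criteria and leaves the participant in therapy has nowhere to go.

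Two things are at stake. First, the non-serious harms count is incomplete by construction, and a reader who relies on the ethics section would take it to be complete. Second, the count mixes two quantities: how often events occur, and how often participants leave because of them. Two arms with the same harm but different retention would show different counts. Deciding that an event caused a participant to stop also takes judgement, in a trial where neither therapists nor participants are blinded (Blinding section).

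**Working it through.** **Setting the passages side by side.** Take an event by whether it is serious and whether it ended treatment.

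| Event | Class under Other outcome measures | Covered by the ethics section's promise |
|---|---|---|
| Serious, treatment ended | Serious | Yes |
| Serious, treatment continued | Serious | Yes |
| Not serious, treatment ended | Non-serious | Yes |
| Not serious, treatment continued | None | Yes |

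Only the last row fails. The section is also at odds with itself there: it presents the non-serious class as the remainder after serious events, then describes something narrower than the remainder.

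**Can the two sections be squared?** Only if the ethics section uses the term adverse event in the narrow sense of the outcome section. The article does not say so. If it were so, the contradiction would disappear but the undercount would stay.

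**Size.** The article states no rate of adverse events and no rate of discontinuation, so what follows is illustration. Let d be the share of non-serious events that stop treatment. Counted share = d; uncounted share = 1 − d.

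- d = 0.05: 1 − 0.05 = 95% uncounted.
- d = 0.10: 1 − 0.10 = 90% uncounted.
- d = 0.20: 1 − 0.20 = 80% uncounted.

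In numbers of events, for 84 participants with an assumed 20% to 50% having one non-serious event each:

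- 20%: 84 × 0.20 = 16.8 events. Counted: 16.8 × 0.05 = 0.84 to 16.8 × 0.20 = 3.36.
- 50%: 84 × 0.50 = 42 events. Counted: 42 × 0.05 = 2.1 to 42 × 0.20 = 8.4.

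**Dependence on retention.** Suppose 30% of the 42 participants in each arm have one non-serious event (assumed): 42 × 0.30 = 12.6 events in each arm, so equal harm. If d is 5% in one arm and 20% in the other, the counts are 12.6 × 0.05 = 0.63 and 12.6 × 0.20 = 2.52. That is a fourfold difference with no difference in harm.

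**The plan's own figure.** The only calculated figure in the article is the sample size: "a standard deviation (SD) = 7, the sample size calculation shows that a total of 84 participants are necessary". With a difference of 5 points, two-sided alpha 0.05, power 0.90 and equal allocation, the normal approximation gives 2 × (1.960 + 1.282)² × 7² / 5² = 41.2, rounded up to 42 per arm, or 84 in total. It reproduces, and nothing in it depends on the adverse-event definition.

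**The case against.** Much can be said for the plan, and it sets firm limits on the point.

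- **The harms table is little more than a discontinuation table.** A reader might infer this. The serious class does not support it: it is broad, reaching events that only might jeopardise the patient, and none of its criteria requires that treatment stopped.
- **An arm that keeps distressed participants in therapy will look safer overall.** The document does not support this either. BDI II and WHO 5 are taken at week 9, and HDRS, BDI II, WHO 5 and SCL 90-R at week 18 and at the 26-week assessment, whether or not the participant stopped. The primary analyses are intention-to-treat, and participants who miss an assessment are invited at least three times. Worsening symptoms would show in the scores. The distortion is limited to the non-serious adverse-event count.
- **Suicidal events are missing from the outcomes.** The Discussion names "quality of life, suicide attempts, suicides" among the outcome measures, and the outcome list does not name the last two. But a suicide is a death, and a suicide attempt would very probably qualify as life threatening or as jeopardising the patient, so both come under adverse events. Both are also collected at every post-randomisation assessment. Nothing is lost.
- **No visit asks about adverse events in general.** The Assessments section lists "use of medication, suicide attempts, and suicides during the intervention period" at weeks 9 and 18, with no general adverse-event item. How events are elicited is something an article may leave to the full protocol, so this is not a fault.
- **Adverse events carry no confirmatory weight.** They are an other outcome, and the error-controlled classes hold only the primary and secondary ones. This stands and limits the consequence.

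What the objections do not remove is the definition. It is a stated rule, not a detail left out for brevity, and as written it leaves a gap.

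**Conclusion.** The point holds in this limited form. The definition of non-serious adverse events excludes every non-serious event that did not stop treatment, contradicts the ethics section on plain reading, and ties the non-serious count to retention. That an undercount arises follows from the wording whenever such an event occurs. Its size is unknown: the 80% to 95% range only restates an assumed discontinuation share of 20% down to 5%, and should not be quoted as an estimate.

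The loss does not reach serious events, suicides, suicide attempts or symptom scores. The primary outcome, its analysis and the total of 84 stand. The point should be corrected because a comparison of non-serious harms between the arms could not be read as such, but it does not threaten the trial's main conclusion.

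**What to change.** In Other outcome measures, delete the last clause of the bracket, the one that makes discontinuation a condition. The non-serious class then covers every adverse event that is not serious, in agreement with the ethics section. Report discontinuation due to an adverse event by arm as a separate line, so that this information is kept without deciding which events count.

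The cost is a change of wording and slightly more recording work. No treatment, visit, analysis of the primary outcome or sample size changes.

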### Description of the outcome assessment instruments

#### HDRS

The severity of a depression can be assessed using the Hamilton Rating Scale for Depression (HDRS) [37]. It is the most commonly used assessment scale for depressive symptoms [8,44,45]. It is a continuous, observer-based assessment method and involves 17 items. Using this scale, the degree of depression is assessed (13 to 17 points = mild depression; 18 to 28 points, = moderate depression; over 28 points = severe depression).

#### SCL 90-R

Symptom Checklist 90 Revised (SCL 90-R) [38] is one of the most commonly used instruments for evaluating psychological and psychopathological symptoms. SCL 90-R is a self-reported questionnaire with 90 items. Each item assesses the degree (0-4) of a symptom during the previous week. Global Severity Index (GSI) derived from the questionnaire is designed to measure overall psychological distress.

#### BDI II

Beck’s Depression Inventory (BDI II) [31]. BDI is self-reported questionnaire with 21 items. The BDI score can be interpreted as: 10–18 mild-moderate depression; 19–29 moderate-severe depression; and 30–63 severe depression.

#### WHO 5

World Health Organisation-Five Well-being Index 1999 (WHO 5) [39] is a self-reported questionnaire that attempts to assess the trial participant’s satisfaction and ‘quality of life’. The questionnaire consists of five items and results in a score between 0 and 100.

#### DAPP-BQ

Personality disorder traits can assessed using the Dimensional Assessment of Personality Pathology-Basic Questionnaire (DAPP-BQ) [41]. It is a self-reported questionnaire involving 290 items and 18 scales.

#### SCID

The Structured Clinical Interviews for DSM-IV Disorders (SCID) is an observer-based diagnostic interview used to determine DSM-IV Axis I disorders (major mental disorders, SCID 1) and Axis II disorders (personality disorders, SCID 2) [30,40].

### Reliability tests for assessment

Two experienced psychologists will perform the Hamilton interviews. During the trial period about 20 of the Hamilton interviews will be rated by both interviewers and the correlation will be presented.

The two members of staff who perform the SCID II interviews will rate five SCID interviews before the trial period begins, and the correlation will be presented.

### Data-management

All data will be stored in the principal investigator’s office and at the Copenhagen Trial Unit. All data will be anonymised on conclusion of the project, i.e., after publication of all results. Privacy of trial participants are protected in accordance with the Act on Processing of Personal Data and the Health Act. The project has been notified to the Danish Data Protection Agency.

All completed HDRS interviews, BDI II, and SCL 90 are sent directly to the Copenhagen Trial Unit for data-management.

### Randomisation

The randomisation will be performed by the Copenhagen Trial Unit. A computer will generate a non-stratified randomisation sequence that will be unknown to the investigators. The randomisation sequence will be generated using a block size unknown to the investigators. A research assistant will randomise by calling the Copenhagen Trial Unit providing a personal pin code and patient number.

### Blinding

The Hamilton psychologist interviewer will be blinded to the treatment allocation and will be instructed to avoid questions beside the Hamilton interview. All interviewees will be instructed not to mention which treatment they have been allocated to. Therefore, the HDRS has been chosen as the primary outcome. It is not possible to blind neither the therapists nor the participants to treatment allocation. A blinded statistician at The Copenhagen Trial Unit will perform statistical analyses with the two intervention groups coded as ‘A’ and ‘B’.

The lead clinical consultant performing the medical consultations will not be blinded to treatment allocation.

All information given to the participants before filling in every questionnaire will be the same for every participant and will be standardised.

### Sample size

With a ‘minimal relevant mean difference’ (MIREDIF) between the two compared interventions of 5 HDRS points, an alpha of 0.05 (type I error), a power of 0.90 (type II error of 10%), and a standard deviation (SD) = 7, the sample size calculation shows that a total of 84 participants are necessary. The calculation is performed using the program “Power and sample size calculations”, version 2.1.31.

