## Design & methods

We will randomise 84 consecutive patients with major depressive disorder 1:1 to one of two interventions:

1. ‘Third wave’ cognitive therapy, approximately n=42.

2. Mentalization-based therapy, approximately n=42.

The inclusion phase is expected to run for about two years.

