### Statistical analyses

The primary analyses will be intention-to-treat (ITT) analyses. Per protocol analyses may also be considered.

Continuous outcomes will be compared between the two intervention groups using the univariate general linear model. If the model assumptions cannot be fulfilled with reasonable approximation a non-parametric test will be used (Mann Whitney). The analysis will be repeated using the baseline variable as a co-variate and the results will be discussed in case of major discrepancies between the two results. Binary outcomes will be compared between the groups using logistic regression. The outcomes will be divided into two classes comprising the primary outcome and all the secondary ones respectively. Dmitrienko et al’s gatekeeping testing procedure with parallel inferences will be used to control the family-wise error rate [46]. All raw P values of all outcome comparisons between the two groups will be presented.

As explorative analyses, all of the above analyses will be repeated with the indicator of comorbid personality disorder as well as the interaction between this indicator and the intervention indicator included. If P of the interaction is ≤ 0.05, an analysis of the corresponding subgroups of patients will be conducted.

If more than 5% of the primary outcome measure is missing, multiple imputation will be used (SPSS version 18 or later). If so, the imputation result will be considered the primary result. This analysis will be supplemented by the following sensitivity analysis. Let A be the group where a beneficial significant effect was observed and B the other group. Missing values in group A will be imputed by the mean value of group B and missing values in group B will be imputed by the mean value of group A. The resulting two distributions will probably not be normal and the variances rather small. So the resulting distributions will be compared using a non-parametric test (Mann-Whitney). This test result will be contrasted to that obtained by comparing the two groups without imputed values also using the non-parametric test.

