We have chosen to classify our control intervention as ‘mentalization-based therapy’. This intervention was, as mentioned, originally designed to treat borderline personality disorder but is now used in a number of different clinical settings symptoms [25,26]. As we except about 80% of the participants will have comorbidity of depression and personality disorder [53], we believe that mentalization-based therapy will be a relevant control intervention. Mentalization-based therapy is a relatively new intervention and we did not identify any relevant treatment manual we could use. We chose to create our own treatment manual, but due to limited resources the mentalization-based manual became relatively short. The content of the control intervention is therefore less strictly defined and this is a further limitation of this trial.

After the initial 18 weeks of intervention, both intervention groups will be offered a follow-up intervention (1 weekly group session). This follow-up intervention will due to limited resources not be manualised and adherence to treatment manual will not be assessed. The results from the follow-up intervention will be difficult to interpret because the form and content of the both follow-up interventions will be unclear. Furthermore, since the participants will be free to leave the trial after the 18 weeks of intensive treatment (before the follow-up treatment begins), it might be unclear if a certain group of patients will be systematically excluded from the analysis and this might cause biased long-term follow-up results. The participants are free to leave the trial at any time point but based on our experience, we expect a relatively large number of participants to be lost to follow up after the 18 weeks of intensive treatment.

Interventions for depression have until now shown relatively small effect sizes. We want to examine two modern psychotherapeutic methods — and we hope that the results from this trial can contribute to new knowledge about effective interventions for depression.

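### The 84 participants are the complete-data sample size: the stated 90% power carries no allowance for missing week-18 HDRS scores, and the article does not say so

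*Protocol article*

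**What the plan says.** The Sample size section of the protocol article gives a minimal relevant difference "between the two compared interventions of 5 HDRS points", "a standard deviation (SD) = 7", "an alpha of 0.05 (type I error") and "a power of 0.90 (type II error of 10"%). It concludes that "the sample size calculation shows that a total of 84 participants are necessary". Design & methods then states: "We will randomise 84 consecutive patients with major depressive disorder 1:1", about 42 per arm. The Abstract gives the same number. The number calculated and the number enrolled are therefore identical.

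Four other places bear on whether every week-18 HDRS will be observed:

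- **Statistical analyses:** "If more than 5% of the primary outcome measure is missing, multiple imputation will be used", and the imputed result then becomes the primary one. A sensitivity analysis for missing values is added.
- **Prevention of missing values:** participants who do not attend are invited at least three times.
- **Discussion:** "The participants are free to leave the trial at any time point". The same sentence goes on to place the relatively large loss that the authors expect after the 18 weeks of intensive treatment.
- **Statistical analyses, on the model:** the main comparison of continuous outcomes is an unadjusted linear model. The version with the baseline value as covariate is a repeat, discussed only if the two differ greatly.

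**The concern.** If 84 is what the formula requires for the analysis, then 84 randomised gives 90% power for the planned unadjusted comparison only with complete data. The article sets out what happens when primary outcomes are missing but does not carry that possibility into the power statement.

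The consequence lies in how a non-significant result is read. The Discussion concedes that earlier systematic reviews found much smaller differences than 5 points between interventions, so such a result is realistic. Readers would then take it to have had a 10% chance of missing a true 5-point difference, when the chance could be higher. The Discussion names the limited sample and the optimistic difference as limitations, but not that the 90% presupposes complete outcome data.

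**Working it through.** **Inputs.** Difference 5, SD 7, alpha 0.05 and power 0.90 come from Sample size; 1:1 allocation comes from Design & methods. The number of sides is not stated. Two-sided is inferred because it reproduces 84, whereas one-sided 0.05 gives 68. The missing rates and correlations below are assumptions, because the article gives none.

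**Step 1: reproduce the plan's figure.** n per arm = 2(z₀.₉₇₅ + z₀.₉₀)²·SD²/difference² = 2 × (1.960 + 1.2816)² × 49/25 = 41.2, rounded up to 42, so 84 in total. This matches with no inflation. At 42 per arm the power is 90.5% by the normal approximation and 89.9% by the noncentral t.

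**Step 2: unadjusted comparison with a fraction m missing.** Complete-case n per arm = 42(1 − m); SE = 7·√(2/n); power from the noncentral t with noncentrality 5/SE; CI half-width = t₀.₉₇₅ × SE.

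| Missing (assumed) | n per arm | SE | Power | 95% CI half-width |
|---|---|---|---|---|
| 0% | 42.0 | 1.53 | 89.9% | 3.04 |
| 5% | 39.9 | 1.57 | 88.3% | 3.12 |
| 10% | 37.8 | 1.61 | 86.5% | 3.21 |
| 15% | 35.7 | 1.66 | 84.5% | 3.31 |
| 20% | 33.6 | 1.71 | 82.2% | 3.41 |
| 30% | 29.4 | 1.83 | 76.8% | 3.66 |

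For comparison, keeping 84 evaluable would need 84/(1 − m) randomised: 89, 94 and 105 at 5, 10 and 20%.

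**Step 3: what multiple imputation could recover.** Above 5% missing, the imputed analysis is the primary one. The Assessments section collects HDRS at baseline, BDI II and WHO 5 at week 9, and BDI II, WHO 5 and SCL 90-R at week 18, all usable as predictors. Suppose they explain a share R² of the HDRS variance and are themselves observed. The effective n per arm is then about 42/[(1 − R²)/(1 − m) + R²]. With an assumed R² = 0.5:

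- m = 10%: 42/(0.5/0.9 + 0.5) = 39.8, power about 88%, against 86.5% for complete cases.
- m = 20%: 42/(0.5/0.8 + 0.5) = 37.3, power about 86%, against 82.2%.

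Recovery is partial. A participant who misses every week-18 measure contributes less than this.

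**Step 4: baseline-adjusted analysis.** The residual SD is 7·√(1 − r²), that is 6.68, 6.42 and 6.06 for r = 0.3, 0.4 and 0.5. Complete-case power:

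| Missing | r = 0.3 | r = 0.4 | r = 0.5 |
|---|---|---|---|
| 0% | 92.4% | 94.2% | 96.2% |
| 10% | 89.5% | 91.7% | 94.3% |
| 20% | 85.6% | 88.2% | 91.5% |

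**The case against.** The strongest case on the other side has five parts.

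- **The 5% rule is a contingency.** A reader might infer that the trial plans for, or expects, more than 5% missing. The rule is conditional, and no week-18 rate appears anywhere. This objection stands.
- **The forecast loss is not at the primary time point.** A reader might apply the relatively large expected loss to the primary outcome. The Discussion places it after week 18. The repeated invitations are there to secure the assessment, and stopping therapy is not the same as missing the HDRS under intention to treat. This stands too. What remains is that earlier withdrawal is allowed and not quantified.
- **Imputation is not worthless.** It would be wrong to say that it restores none of the lost information: step 3 shows partial recovery. Equally, it does not bring power back to the complete-data figure.
- **The arithmetic is right, and this is a condensed article.** The stated number does reproduce exactly. But the article gives all its inputs, and the number calculated equals the number randomised. The lack of margin is therefore visible in what is printed and does not depend on something left to a fuller document.
- **The effect is small at the one rate the article mentions.** At 5% missing the loss is 1.6 points (89.9 to 88.3). An SD of 7.5 in place of 7 would cost more with complete data (85.5%). This stands: the loss becomes material only from about 10%, which is an assumed rate.

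The documents also do not show what power was put to the ethics committee. The Ethical considerations section records approval only, so nothing can be said on that.

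**Conclusion.** The point holds in a limited form. The calculation contains no error, but 84 is the complete-data number and the trial randomises exactly that many. The stated 90% for the unadjusted comparison is therefore a ceiling that the article presents without qualification. Under assumed missing rates of 5, 10 and 20%, complete-case power is about 88, 87 and 82%. At 20% the type II error is nearly 18%, against the stated 10%. Imputation would soften this by an amount that depends on how well the other scores predict HDRS.

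The 90% is not out of reach once any score is missing. The baseline-adjusted analysis exceeds it at 10% missing if r is 0.4 or more, and at 20% if r is about 0.5. As planned, however, that analysis is only a repeat, so its gain does not reach the main comparison. Nor do the documents support saying that the trial will fall short of 90%, since they give no week-18 missing rate. They support saying that no margin was provided and that the power statement omits its condition.

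**What to change.** Keep 84 and make two changes.

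1. **Sample size.** Restate the power as 90% with complete week-18 HDRS data, and about 82-88% for the unadjusted comparison if 5-20% of scores are missing, labelled as an assumed range. If the sponsor has an expected week-18 rate, give the power at that rate. Add the expected 95% CI half-width, about 3.0-3.4 points over 0-20% missing, so that a non-significant result is read against the 5-point difference.
2. **Statistical analyses.** Make the already planned analysis with baseline HDRS as covariate the primary one and the unadjusted model the supporting one. State its power over a range of assumed correlations: at 20% missing, about 86, 88 and 91% for r = 0.3, 0.4 and 0.5.

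The first change costs two sentences and a slightly less favourable power figure. The second alters which analysis is primary, so it should be declared as a change and fixed before the coded groups are analysed. It needs no new data, because baseline HDRS is already collected. Neither change adds enrolment.
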